### Physiological subgroup

2.8

To complement self-reported outcomes with physiological data, the study includes an optional physiology component for a subset of participants. Up to 15 participants per group (approx. n≈90 total) who live in the Berlin/Brandenburg region will be invited to attend laboratory sessions at the Charité – Virchow Clinic Campus in Berlin. Electrophysiological measurements will be performed over a 15-min period during which the participant is at rest and in a supine position in the electrophysiological laboratory. During this period, the ECG and pulse are recorded using wearables. Electrophysiological measurements are to be recorded at two time points: initially at the baseline (T0) and subsequently following the six-week intervention period (T1). The ECG and pulse raw data indices were utilized to derive HRV and pulse wave variability (PWV), which are indices of autonomic nervous system (ANS) activity. The activity of the sympathetic nervous system (SNS), the parasympathetic nervous system (PNS), or both components of the ANS is indicated by these indices. In the course of each and every recording session, the participants were equipped with a Polar H10 chest-strap heart rate sensor (for the purpose of recording ECG for HRV) and a Polar Verity Sense optical pulse sensor (for the purpose of PWV via photoplethysmography). It is hypothesized that the response to the various 6-week interventions would be subject to change, and that the before-and-after effect would vary in the autonomous variables depending on the nature of the intervention. This methodology facilitates the representation of variation in dynamic changes across groups and over time. A comparison of the time points T0 and T1 will facilitate objective and quantitative mapping of the dynamic changes caused by the interventions. The autonomous measurements will facilitate the characterization of the interventions in terms of their mechanisms of action, and the extent to which each intervention leads to the assumed subjective improvement in relaxation/recovery (increased PNS). In addition, the study will elucidate the way this intervention enhances autonomic-vegetative function in the short term. The utilization of HRV and PWV in the time domain, in the frequency domain and nonlinear dynamics, has been demonstrated to be a reliable indicator of changes in sympathovagal balance (19). A greater HRV (particularly high-frequency HRV) and a slower PWV (which reflects vasodilation and reduced arterial stiffness) would suggest a shift towards parasympathetic dominance and relaxation. It is hypothesized that the combination of hypnosis and essential oils may result in increased relaxation, which is further enhanced by the intervention and over time from T0 to T1 in comparison to the hypnosis-only group. This is consistent with the hypothesis that deeper or more effective relaxation training is achieved through this method. The resultant phenomenon is evidenced by a decline in sympathetic tone and an augmentation in vagal tone, culminating in a state of profound relaxation and recuperation through the deactivation of the ANS.

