**Exploratory Hypothesis 2.3 (Moderators of Effect).** We will explore whether certain baseline factors moderate the intervention's effectiveness. Demographic factors like age, gender, or socioeconomic status might influence outcomes. For instance, it's possible that participants with higher initial anxiety, though still subthreshold, benefit more or less from the intervention, or that younger vs. older participants have different adherence rates. These analyses are exploratory and will be used to generate hypotheses for which subgroups respond best to this approach.

**Exploratory Hypothesis 2.4 (Physiological Effects).** We hypothesize that the combination of hypnosis and aromatherapy yields measurable physiological relaxation, reflected in increased parasympathetic activity or reduced sympathetic activity compared to hypnosis alone. In the laboratory subgroup, it is hypothesized that Group 1/2 (combined) will demonstrate larger increases in HRV, particularly high-frequency HRV, which is indicative of parasympathetic tone, and/or a greater reduction in heart rate and PWV from T0 to T1 than Group 3 (hypnosis only). This would suggest an additive effect of the essential oil on the body's relaxation response, consistent with objective evidence that an essential oil can modulate autonomic activity. However, given sample size limitations, this will be an exploratory outcome.

**Exploratory Hypothesis 2.5 (VAS Trajectory and Learning Effects).** By examining the VAS relaxation ratings collected before and after each session, we hypothesize that participants receiving the combined intervention will not only have larger acute relaxation gains per session on average than those in comparison groups, but they may also exhibit learning effects over time. A learning effect would manifest as gradually higher pre-session relaxation levels as weeks progress the participant's baseline state before each session improves, indicating they carry over some relaxed state or become more skilled at self-relaxation. We expect such effects might be most pronounced in those who undergo conditioning (Groups 1 and 2), potentially showing an upward drift in pre-session VAS scores and/or a plateau indicating habituation to relaxation. We will explore and graph these trajectories for insight into how the relaxation response develops with practice.

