### Biosignal processing

2.12

A total of 15 min of ECG (130 Hz) and photoplethysmographic (PPG; 28 Hz) data will be collected from all participants of the sub-study during the resting conditions at T0 and T1. The ECG data will be recorded using a Polar H10 chest-strap, and the PPG data will be recorded using a Polar Verity Sense optical pulse sensor. The participants will remain in a seated position during the recording. The time series estimating functions of the autonomic regulation will be semi-automatically extracted from the raw data using Kubios HRV Scientific Software for the ECG and an in-house software (programming environment Matlab R2025a) for the PPG, derived as follows:
time series of heart rate, consisting of successive beat-to-beat intervals [BBI, (ms)],time series containing maximum PPG peak amplitudes per heartbeat [PPGMAX, (a.u.)], andtime series containing minimum PPG peak amplitudes per heartbeat [PPGMIN, (a.u.)].Afterwards each 15-min time series will be filtered by applying an adaptive variance estimation algorithm to remove and interpolate ectopic beats and artefacts to ensure normal-to-normal time series (NN) (21). Afterwards indices describing autonomic regulation will be calculated in the time domain (TD), in the geometric domain [Baevsky's stress index (22)], the frequency domain (FD) (the power spectra of equidistant linear interpolated NN interval time series will be obtained by applying the Fast Fourier Transformation), and in the nonlinear domain (NLD) (Table 1).

**Table 1 T1:** Definition of clinically relevant HRV indices and their assignment to the autonomic nervous system.

Domain	Index	Unit	Definition and explanation	Activity as part of the autonomic nervous system
Time domain	meanNN	ms	Mean value of all NN intervals	—
	SDNN	ms	Standard deviation of NN intervals in the measurement time range	Sympathetic nervous system and parasympathetic nervous system
	SDANN	ms	Standard deviation of the average of NN intervals in 5-min segments	Sympathetic nervous system and parasympathetic nervous system
	RMSSD	ms	“Root Mean Square of successive differences” (Square root of the mean value of the sum of all squared differences between adjacent NN intervals)	Parasympathetic nervous system
	NN50	beats	Number of pairs of adjacent NN intervals that differ by more than 50 ms	Parasympathetic nervous system
	pNN50	%	Percentage of consecutive NN intervals that differ by more than 50 ms	Parasympathetic nervous system

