Geometric	SI		Stress Index, square root of Baevsky stress index, reflects cardiovascular stress	Sympathetic nervous system
Frequency domain	TP	ms^2^	Total Power: Total power or total spectrum; corresponds to energy density in the spectrum from 0.00001 to 0.4 Hz (VLF, LF and HF)	No clear assignment
	VLF	ms^2^	“Very low frequency power” (Power density spectrum in the frequency range of 0.003–0.04 Hz)	Parasympathetic nervous system
	LF	ms^2^	“Low frequency power” (Power density spectrum in the frequency range of 0.04–0.15 Hz); LFn [n.u.]	Sympathetic and parasympathetic nervous systems, with the parasympathetic nervous system predominating
	HF	ms^2^	“High frequency power” (Power density spectrum in the frequency range of 0.15–0.40 Hz); HFn [n.u.]	Parasympathetic nervous system
	LF/HF	—	Ratio of LF and HF	Sympathetic-parasympathetic balance
Nonlinear dynamics Poincaré-Plot	SD1	ms	Standard deviation of the point distances to the transverse diameter	Parasympathetic nervous system
	SD2	ms	Standard deviation of the point distances to the longitudinal diameter	Sympathetic nervous system and parasympathetic nervous system

In NLD most prominent measures will be applied describing important features such as nonlinearity, time irreversibility, fractality, and long-range correlations of physiological dynamics. As one example described in more detail, Symbolic dynamics (SD). The idea of SD is based on simplifying the non-linear dynamics (the way things change over time) that are part of time series (23). Consequently, the NN will be transformed into a symbol sequence of four symbols with a given alphabet *A* = {0, 1, 2, 3}. The creation of words from this new alphabet (consisting of a symbol string) will be achieved through the utilization of three successive symbols, thereby enabling 64 distinct word-type combinations (bins) (000, 001,…,333). The following SD indices from the probability distribution of each word-type within the symbol sequence will be estimated:

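### Linear interpolation of the NN series before the FFT understates HF power by an amount that depends on heart rate and breathing, distorting HF, HFn and LF/HF (minor; exploratory indices only)

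*Protocol article*

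**What the plan says.** Section 2.12 (Biosignal processing) describes the recording: "A total of 15 min of ECG (130 Hz) and photoplethysmographic (PPG; 28 Hz) data will be collected" at T0 and T1. After artefact filtering, the frequency-domain step is stated outright: "the power spectra of equidistant linear interpolated NN interval time series will be obtained by applying the Fast Fourier Transformation". No correction for the frequency response of the interpolation is mentioned.

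Table 1 defines LF as 0.04-0.15 Hz and HF as 0.15-0.40 Hz, each in ms² and in normalised units. It also lists total power and LF/HF. HF is assigned to the parasympathetic system.

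Exploratory Hypothesis 2.4 (section 2.10) expects, in the combined arms compared with hypnosis alone, "larger increases in HRV, particularly high-frequency HRV, which is indicative of parasympathetic tone, and/or a greater reduction in heart rate". Section 2.8 also names high-frequency HRV as the main sign of a parasympathetic shift. The sub-study has up to 15 participants per group, and sections 2.8 and 2.10 both call it exploratory. Only ECG and pulse are recorded; no respiratory signal is listed.

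**The concern.** NN intervals arrive once per beat, so the series is sampled about once a second. The HF band lies close to the limit of what that spacing can carry. Straight lines between the points flatten the respiratory oscillation, and more so when beats are further apart or breathing is faster. The slower LF oscillation is barely touched.

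Three things follow for the index that Hypothesis 2.4 singles out:
- HF in ms² is too low.
- LF/HF and the normalised units are shifted towards apparent sympathetic dominance.
- Measured HF depends partly on heart rate, which the intervention may itself change, and on breathing rate, which is not measured.

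This is a choice that the article makes in its own text, not a detail left to another document.

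**Working it through.** The plan states no figure for this loss, so there is none to reproduce.

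**Inputs from the protocol article.** Linear interpolation then FFT (2.12); LF 0.04-0.15 Hz and HF 0.15-0.40 Hz (Table 1); up to 15 per group (2.8).

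**Assumptions, not in the documents.** Resting heart rate 60-75 bpm; breathing frequency 0.20, 0.25 or 0.30 Hz; LF peak at 0.1 Hz.

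**Formula.** With mean NN interval T = 60/HR seconds, linear interpolation has amplitude response sinc²(fT). The power retained is sinc^4(fT), where sinc(x) = sin(πx)/(πx) and fT = f_resp/f_heart.

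**Worked case, 70 bpm and 0.25 Hz.** T = 0.857 s and fT = 0.214. Then sinc = 0.926 and sinc^4 = 0.736, a loss of 26.4%.

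**Loss of power under linear interpolation:**

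| HR (bpm) | LF, 0.10 Hz | 0.20 Hz | 0.25 Hz | 0.30 Hz |
|---|---|---|---|---|
| 60 | 6.4% | 23.4% | 34.3% | 45.7% |
| 65 | 5.5% | 20.3% | 30.0% | 40.4% |
| 70 | 4.7% | 17.7% | 26.4% | 35.9% |
| 75 | 4.1% | 15.6% | 23.4% | 32.1% |

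For a flat spectrum across the whole HF band, the loss is 28-40% over the same heart rates.

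**Check by simulation.** Beat series of 15 minutes were resampled at 4 Hz and analysed by Welch FFT, 30 runs per setting. The linear results agreed with the formula to about half a percentage point. A cubic spline on the same beats, at 60-75 bpm, lost 0.4-1.1% at 0.20 Hz, 1.1-3.1% at 0.25 Hz and 2.5-7.5% at 0.30 Hz.

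**Effect on LF/HF and HFn.** At 65 bpm and 0.25 Hz, LF/HF is multiplied by 0.945/0.700 = 1.35. Over 60-75 bpm at 0.25 Hz, the factor runs from 0.936/0.657 = 1.42 down to 0.959/0.766 = 1.25. If HFn is taken as HF/(LF+HF) and the true powers are equal, HFn reads 0.700/(0.945+0.700) = 0.43 instead of 0.50 at 65 bpm.

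**Part that can differ between visits or arms.** Take no true change in HF and breathing fixed at 0.25 Hz:
- 70 to 67 bpm: 0.715/0.736 = 0.972, a fall of 2.8%.
- 70 to 65 bpm: 0.700/0.736 = 0.951, a fall of 4.9%. At 0.20 Hz the fall is 3.1% and at 0.30 Hz it is 7.0%.
- With the spline, 70 to 65 bpm gives (1 - 0.021)/(1 - 0.014) = 0.993, a fall of 0.7%.

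Now let breathing slow as well, for 70 to 67 bpm:
- In proportion to heart rate: fT is unchanged, so there is no effect.
- From 0.25 to 0.233 Hz: measured HF rises by 1.6%.
- From 0.25 to 0.22 Hz: measured HF rises by 4.9%.

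**The case against.** A reader might infer that the method works against Hypothesis 2.4, because it would lower measured HF in the arms where heart rate is expected to fall. The documents do not support that. The loss depends on the ratio of breathing to heart rate, so the direction holds only if breathing frequency stays the same. A relaxation intervention may well slow breathing, and no respiratory data are planned. Nor does the hypothesis commit to both changes at once: it joins the HRV rise and the heart-rate fall by and/or. This part of the objection stands in full.

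It is also fair that the loss of roughly a quarter to a third at 0.25 Hz is not the size of any bias in a group comparison. It is largely shared by both visits and all arms and mostly cancels in relative or log changes. Only a between-arm difference in heart-rate or breathing change leaves a residue, and that is small. Suppose the SD of change in ln HF is 0.5-0.8 (an assumption). With 30 participants in Groups 1 and 2 against 15 in Group 3, the standard error is SD × √(1/30 + 1/15), or 0.16-0.25. A differential fall of 3-5 bpm from 70, with breathing fixed at 0.25 Hz, gives 0.03-0.05 log units, about 0.1-0.3 of a standard error.

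Finally, the vagal reading does not rest on HF alone. RMSSD, NN50, pNN50 and SD1 do not pass through this step, and meanNN is reported.

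These points limit the weight of the finding without removing it. Table 1 gives HF in ms² and no log scale is stated. LF/HF and the normalised units are distorted on any scale. Without a respiratory signal, the dependence on breathing cannot be checked afterwards.

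**Conclusion.** The point holds as a minor one. Under the stated assumptions (60-75 bpm, breathing at 0.20-0.30 Hz), the specified method understates HF power by 16-46%, with 23-34% at 0.25 Hz, against 4-6% for LF at 0.1 Hz. At 0.25 Hz this inflates LF/HF by about 25-42%; HFn is deflated. Differences in HF expressed in ms² shrink by roughly the lost share.

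What does not cancel between visits or arms is a dependence on heart rate and breathing. It amounts to a few per cent for heart-rate changes of 3-5 bpm, and its sign for Hypothesis 2.4 is undetermined. Only the exploratory frequency-domain indices are touched: HF, LF/HF, LFn, HFn and, through HF, total power. The primary MDBF analysis, the sample size and the time-domain and Poincaré indices are not.

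**What to change.** In section 2.12, replace linear interpolation with cubic-spline interpolation at a fixed rate (for example 4 Hz) before the FFT. Alternatively, apply a Lomb-Scargle periodogram to the unevenly spaced NN series, which avoids interpolation. Use the same method at T0 and T1.

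The spline does not remove the loss entirely. At slow heart rates with fast breathing it still matters: in the simulation it lost 18.9% at 50 bpm and 0.30 Hz, against 58.5% with linear interpolation. Over the assumed resting range it removes most of it.

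The cost is one phrase and a software setting. No new data, visits or participant burden are needed, and the change can be applied to stored recordings, provided it is fixed before the analysis.

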#### Procedure

2.5.1

In Phase 1 (weeks 1–6), participants practice digital self-hypnosis every two days (approx. 3–4 sessions per week) using audio recordings delivered through the SoSci web interface. Each session involves listening to a guided hypnosis audio; the first session is ∼22 min long, and subsequent sessions last ∼11 min each. The hypnosis script focuses on inducing relaxation and calm, those used in the earlier study (11), and it is standardized across participants aside from the experimental manipulations of essential oil. Participants are instructed to find a quiet, comfortable place for each session and to listen to the audio using headphones or speakers without interruption.

Simultaneously, groups 1, 2, 5, and 6 combine these hypnosis sessions with aromatherapy using an essential oil. Those assigned to an aromatherapy condition receive a small aroma stick (inhaler) infused with either Lavender essential oil or Bergamot essential oil, depending on group, to use during the sessions. They are instructed to inhale from the aroma stick at the beginning of each hypnosis session and intermittently breathe in the fragrance as needed throughout the audio, allowing the olfactory stimulus to be present during the hypnotic relaxation. By pairing the specific essential oil with the hypnosis-induced relaxation repeatedly over 6 weeks, the intervention seeks to create a strong mental association between that smell and the relaxed state.

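### High-frequency HRV is read as a sign of relaxation with no check of breathing rate, so slow breathing at T1 could hide or reverse an effect on that index

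*Protocol article*

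**What the plan says.** Table 1 in section 2.12 (Biosignal processing) gives HF as "Power density spectrum in the frequency range of 0.15–0.40 Hz" and assigns it to the parasympathetic nervous system. LF is "Power density spectrum in the frequency range of 0.04–0.15 Hz", assigned to both branches with the parasympathetic branch predominating. LF/HF is labelled as sympathetic-parasympathetic balance.

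The reading rule is in section 2.8 (Physiological subgroup): "A greater HRV (particularly high-frequency HRV) and a slower PWV" would suggest parasympathetic dominance and relaxation. For the change between T0 and T1, Hypothesis 2.4 in section 2.10 predicts in Groups 1/2, against Group 3, "larger increases in HRV, particularly high-frequency HRV, which is indicative of parasympathetic tone, and/or a greater reduction in heart rate and PWV".

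On the signals, section 2.12 states: "A total of 15 min of ECG (130 Hz) and photoplethysmographic (PPG; 28 Hz) data will be collected". It goes on to posture, software, artefact filter, interpolation and spectral method. Neither it nor any other section mentions a respiration signal, paced breathing, or any use of breathing rate in reading HF or LF/HF.

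**The concern.** Breathing-related vagal modulation of heart rate appears in the spectrum at the breathing frequency. A fixed HF band captures it only while the participant breathes within that band. Someone who breathes more slowly than the lower edge keeps the modulation, but it is counted as LF. HF falls and LF/HF rises with no vagal loss.

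Slower breathing is a plausible companion of successful relaxation training. The index that the plan emphasises could then stay flat or move the wrong way in the very participants who respond. With up to 15 participants per group, a few such recordings could decide how the HF result looks, and without breathing rates nobody could tell afterwards what had happened.

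**Working it through.** The article states no sample size, power or effect size for Hypothesis 2.4, so there is no planned figure to reproduce. The check concerns the band limits and their consequence.

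**1. Band limits in breaths/min** (Hz x 60, limits from Table 1)
- HF: 0.15 x 60 = 9 and 0.40 x 60 = 24, so 9-24 breaths/min.
- LF: 0.04 x 60 = 2.4, so 2.4-9 breaths/min.

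**2. What happens below 9/min with unchanged modulation.** Simulated 15-min NN series: mean NN 900 ms, respiratory amplitude 40 ms at every rate, 1/f background SD 20 ms, linear interpolation at 4 Hz, Welch spectrum. Everything except the 15-min length, the linear interpolation and the Fourier basis is an assumption. Breath-to-breath variation (CV) was set to 5%, 15% and 25%. Mean HF power in ms², with change against 12/min:

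| Breaths/min | CV 5% | CV 15% | CV 25% |
|---|---|---|---|
| 12 | 704 | 661 | 604 |
| 9 | 368 (-48%) | 374 (-43%) | 327 (-46%) |
| 8.5 | 83 (-88%) | 210 (-68%) | 292 (-52%) |
| 8 | 63 (-91%) | 134 (-80%) | 218 (-64%) |
| 6 | 51 (-93%) | 63 (-90%) | 76 (-87%) |

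LF/HF between 12/min and 8/min:
- CV 5%: 103/704 = 0.15 to 814/63 = 12.9
- CV 15%: 133/661 = 0.20 to 743/134 = 5.5
- CV 25%: 202/604 = 0.33 to 660/218 = 3.0

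RMSSD between the same rates, at CV 15%, goes from 34.0 to 25.8 ms. That is a fall of 8.2/34.0 = 24%; it is 25% at CV 5% and 23% at CV 25%. SDNN does not change.

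Sensitivity of the losses: a 20% second harmonic makes the loss at 6/min 82-89%. With no background at all, which is an extreme case, the loss at 8.5/min is 64-96%.

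**3. One slow breather in a group of 15** (maximum group size from section 2.8). Shift in mean ln HF = ln(1 - loss)/15.
- Loss 52%: ln(0.48)/15 = -0.734/15 = -0.05
- Loss 93%: ln(0.07)/15 = -2.659/15 = -0.18

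**4. Shift for a whole group.** Assume normally distributed breathing rates with SD 3/min and a mean falling from 15 to 13 or 12. Share below 9/min:
- Mean 15: z = -2.00, 2.3%
- Mean 13: z = -1.33, 9.1%
- Mean 12: z = -1.00, 15.9%

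The share rises by 6.8 or 13.6 percentage points. Proportional fall in geometric-mean HF = 1 - exp[(rise in share) x ln(1 - loss)]:
- Smallest: 1 - exp(0.068 x -0.734) = 5%
- Largest: 1 - exp(0.136 x -2.659) = 30% (31% if the shares are first rounded to 2% and 16%)

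The largest figure gives everyone below 9/min the loss seen at 6/min with very regular breathing. In a normal tail most of these people sit just below 9/min, so the lower half of the range is more realistic.

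**The case against.** Four arguments on the other side have force.

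*The article is condensed and the band is standard.* Both are true. A missing breathing covariate alone would not be a finding, because a full protocol or SAP may hold it. What remains is that the article itself states the rule that higher HF means relaxation, and does so without the condition under which the rule works.

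*HF is not the only index.* Correct. Hypothesis 2.4 also names heart rate and PWV, joined by and/or. Table 1 lists RMSSD, NN50, pNN50 and SD1 as parasympathetic. A reader might infer that the hypothesis stands or falls with HF; the text does not say so. These other indices soften the problem but do not remove it: RMSSD also drops with slow breathing, and nothing says how to read HF and RMSSD if they disagree.

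*All three arms in the contrast receive hypnosis, and recordings are at rest, away from sessions.* Slowing common to Groups 1, 2 and 3 largely cancels. One might argue that the oil arms slow more because they "intermittently breathe in the fragrance as needed throughout the audio" (section 2.5.1). That is not breathing training, and the documents do not show that it lowers later resting breathing rate. Differential slowing is therefore a possibility only. Cancellation does not, however, protect the T0-T1 changes within groups, which section 2.8 also interprets, or comparisons with Group 4, which has no hypnosis.

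*The analysis is exploratory.* Sections 2.8 and 2.10 say so, which keeps the point minor.

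**Conclusion.** The point holds as a minor one. The plan reads fixed-band HF as parasympathetic tone with no check that breathing lies within the band. If participants breathe below 9/min at T1, a relaxation effect can be missed or appear reversed on HF. With modulation unchanged, the HF loss is about half to nine-tenths, depending on rate and regularity. One such person in 15 shifts mean ln HF by about -0.05 to -0.18, and an assumed slowing of 2-3/min lowers geometric-mean HF by about 5-30%. These figures rest on simulation settings and breathing rates that are not in the documents. If breathing does not slow there is no bias, and if it slows equally in the compared arms the contrast between them is not biased.

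Two stronger readings are not supported. One is that anyone below 9/min loses almost all HF power: at 8.5/min with irregular breathing the loss is about half. The other is that the plan would report a vagal effect as sympathetic: Table 1 calls LF predominantly parasympathetic and gives LF/HF no direction. No primary or secondary conclusion of the trial is affected.

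**What to change.** Specify the following before the physiological data are analysed.

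1. Derive breathing frequency from the ECG already recorded at T0 and T1. Report it by group, with the number of recordings whose respiratory peak is below 0.15 Hz.
2. Keep the planned HF analysis. For recordings with a peak below 0.15 Hz, state that HF and LF/HF are not read as vagal or balance measures, and read the already planned RMSSD and SD1 alongside them.
3. Add, as a sensitivity analysis only, ln HF adjusted for breathing frequency or computed in a band centred on each person's breathing frequency. It should not become the main analysis: T1 breathing rate arises after randomisation and may be part of the effect, so adjusting for it could remove real benefit.

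The cost is a little more analysis work, with no new visits or sensors. ECG-derived respiration is less exact than a respiration belt, so recordings close to 9/min will be classified with some error.
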